### Heterogeneity of Treatment Effects Analysis:

This analysis, part of the mixed model longitudinal data detailed above, will assess the interaction of age (years at randomization) and tear size (cm) with treatment on  $\Delta\text{SPADI}_{12}$ . The covariate set for the adjusted mixed models is defined in section 12.2.1. Table 1 depicts an example of a binary covariate interaction with treatment with a contrast effect size at the MCID = 10 – 15 – 30 + 45=10. The standard general contrast variance assuming common variance among groups and equal cell size =  $\sigma^2[\sum_{i=1}^k(\frac{c_i^2}{n_i})]$ . These elements form the basis for the interaction sample sizes in figure 4.

| Table 1. Example Table of Average 12-Month Change in SPADI from Baseline where the Interaction Effect is the MCID |         |         |
|-------------------------------------------------------------------------------------------------------------------|---------|---------|
| Treatment                                                                                                         | Group 1 | Group 2 |
| Non-operative                                                                                                     | 10      | 15      |
| Operative                                                                                                         | 30      | 45      |

### 12.2.2 Secondary Analyses

Secondary analyses will be based a more general model denoted,

$$y_{ij} = \beta_0 + \beta_1 I_{\{TRT_i=Op\}} + \beta_2 t_{ij} + \beta_3 I_{\{TRT_i=Op\}} t_{ij} + \gamma Z_i + u_i + e_{ij}$$

where  $y_{ij}$  represents the change in ASES-SF (or any other outcome metric) from baseline for participant  $i = 1, \dots, n$  at time  $j = 3, 6, 12$  months who was assigned to management arm  $TRT_i$  ( $I_{\{TRT_i=Op\}} = 1$  if participant  $i$  is on the Operative arm and 0 otherwise) and who has a  $k$ -dimensional vector of covariates  $Z_i$  (e.g., gender, mental health inventory, fatty infiltration, etc.) with effect parameters  $\gamma_k$ .  $\beta_0$  is the intercept, and  $\beta_3$  is differential change in ASES score over time due to treatment (i.e., the treatment effect over time; assumed linear here but it will be modeled flexibly as needed). As in section 12.2.1, the last 2 terms represent a patient specific random intercept and residual error, respectively. The estimate of interest from this longitudinal model is the predicted differential in 12-month ASES-SF

change ( $\Delta\Delta\text{ASES-SF}_{12}$ ; 1st  $\Delta$  is for treatment change, 2nd  $\Delta$  is for 12-month change), which is typically estimated as a contrast or difference in predicted 12 month ASES-SF change.

Similar to the setting described in section 12.2.2 directly parallel analyses will also be conducted, where  $y_{ij}$  represents ASES-SF (or other secondary outcomes) for participant  $i = 1, \dots, n$  at time  $j = 3, 6, 12$  months with baseline ASES-SF as a covariate. Differential inference between these two sets of models was described above.

## 12.3 Sample Size Considerations

### 12.3.1 Primary Aim

A longitudinal mixed model will be used to compare the 12-month change in SPADI between treatment arms. The operating characteristics of this plan depend on the marginal distribution of  $\square\text{SPADI}_{12}$ , the assumed true distributional shift, and observed covariate patterns. Figure 3 displays the marginal distribution of  $\square\text{SPADI}_{12}$  for patients by treatment group. These distributions were derived from preliminary data taken from an ongoing prospective, non-randomized cohort of patient with degenerative rotator cuff tears receiving either non-operative or operative intervention. The mean  $\square\text{SPADI}_{12}$  was -16.7 (SD=24.2; n=72) overall. Current estimates for non-operative therapy are -12.3 (SD=21.55; n=45) and -40.6 (SD=19.14; n=27).

### 12.3.2 Effect Size and Alternative Hypotheses

A 10 unit change in SPADI is the smallest clinically meaningful change. In Aim 1 we test the null hypothesis that  $\square\text{SPADI}_{12}$  for patients treated operatively versus non-operatively is equal. As shown below, a sample size of 700 provides outstanding power to detect a 10-unit difference between treatment arms in 12-month SPADI change from baseline.

[figure not shown]

Figure 3. Distributions of 12-month change in SPADI by treatment group.

### 12.3.3 Sample Size Projections

A sample size of 700 participants (350 per treatment group) provides excellent power even with significant levels of dropout/lost-to-follow-up rate (a two-sided Type I Error of 0.05 was used). Figure 4 illustrates the power for three different tests of  $\Delta\Delta\text{SPADI}_{12}$ . The black line shows the power for a simple t-test of 12-month SPADI change scores between treatment groups. The red line shows the power for a least squared means Wald test of the 12-month SPADI change scores between groups, but adjusted for baseline

covariates (mixed model with complete case analysis). The blue line shows the power for the same test from the mixed model, but when multiple imputation is used to properly account for the large number of missing observations in the preliminary data (RVI is 0.53). Here, RVI is the average relative increase (averaged over all coefficients) in variance estimates due to missing values. The largest fraction of missing information (FMI) is 0.412. Interestingly, rather than gaining efficiency, the MI mixed

model appears less efficient. Because the MI model properly accounts for variability in the presence of missingness, we can use this model to anticipate a loss of power due to missing data. These curves are based on the estimated standard deviation from the preliminary data: (black) t-test on available data, (red) mixed model on complete case data, (blue) multiply imputed mixed model. The dotted line shows the power to detect the same minimally clinically meaningful change in binary subgroups across treatment groups (e.g., gender by treatment interactions). The standard deviations for these curves were similarly derived from preliminary data. This approach allows us to carefully leverage preliminary data to anticipate cluster correlation, covariate effects, missing data patterns, and longitudinal correlation patterns. These projections are conservative.

To be clear, power for the adjusted mixed model reaches 90% at 60 patients per group. With the increased variance from imputation, power reaches 90% with 82

[figure not shown]

**Figure 4.** Power curves for primary treatment comparison (solid lines) and interactions (dashed lines) from covariate adjusted

patients in each treatment group. For the unadjusted t-test, 90% power is achieved with 91 patients per treatment group. For the subgroup/patient heterogeneity analyses, 80% power to detect a 2-way interaction as small as the MCID is achieved with 122 patients per group (total n=488) for the imputed data set. Consequently, we expect to have excellent power to detect heterogeneous treatment effects, even in the presence of significant missing data (FMI was 0.41). Lastly, we note that in our preliminary data, the intraclass correlation coefficient (ICC) for institution was 0.04 (essentially zero) and largely inconsequential given the longitudinal correlation in SPADI measurements. If necessary, our approach permits the sequestering of site-to-site variability from residual error, increasing power for detecting fixed effects in the data.

#### **12.3.4 Safety Review**

A continuous monitoring rule for monitoring SAE has been developed for the DSMC to ensure the SAE rate does not exceed 10%.

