## **9 ASSESSMENT OF SAFETY**

### **9.1 Specification of Safety Parameters**

The operative and non-operative treatments in this trial are standards of usual care. The Adverse Events (AEs) and Serious Adverse Events (SAEs) are therefore those inherent to standard of care treatments. Safety parameters will be recorded in our online data capture system (REDCap). These parameters include the date of occurrence of AE/SAE, a detailed description of the nature of the event, assessment, follow up, and the resolution of the AE/SAE, as appropriate to the event. The safety procedures will be performed for our primary study/trial that ends at one (1) year of follow up and not for the sub-study. Further details are provided in the sections below.

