#### **9.1.3 Serious Adverse Events (SAEs)**

SAEs for this trial include:

- Death
- Event requiring hospitalization (in-patient admission) related to treatment

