## **9.4 Reporting Procedures**

### **9.4.1 Related SAEs & Safety Issues**

The following will be reported to the IRB, the funding agency (PCORI), and the DSMC within 7 calendar days of the PI becoming aware of the event:

- Any serious adverse event that in the investigator's opinion was unanticipated or unexpected, involved risk to participants or others, and was possibly related to the research procedures
- Any noncompliance with the IRB-approved protocol that increased risk or affected the participant's rights, safety, or welfare.

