### **9.4.2 AEs & Unrelated SAEs**

Anticipated AEs or unrelated SAEs will be handled in a less urgent manner but will be reported to the DSMC, IRB, and funding agency (PCORI). All individual AE and Safety reports will be maintained by the investigator and a summary (not individual reports) of all adverse events that have occurred within the last approval period that are associated with the study, whether related or non-related, will be submitted to the IRB at the time of continuing review. These reports will also be submitted to the DSMC and the funding agency (PCORI) during the yearly DSMC meetings.

Adverse events may include a participant's death as a result of a longtime illness (non-related), a breach in confidentiality, or any complaint of a participant unless the risk involved is serious (in which case, the event is reported as an unanticipated problem involving risk to participants or others or as a serious adverse event at the time of occurrence).

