### **9.4.3 Unanticipated Problems**

Incidents or events that meet the OHRP criteria for unanticipated problems will be recorded in an event report form. The following information will be included when reporting an adverse event, or any other incident, experience, or outcome as an unanticipated problem to the IRB:

- appropriate identifying information for the research protocol, such as the title, investigator's name, and the IRB project number;
- a detailed description of the adverse event, incident, experience, or outcome;
- an explanation of the basis for determining that the adverse event, incident, experience, or outcome represents an unanticipated problem;
- a description of any changes to the protocol or other corrective actions that have been taken or are proposed in response to the unanticipated problem.

To satisfy the requirement for prompt reporting, unanticipated problems will be reported using the following timeline:

- Unanticipated problems that are serious adverse events will be reported to the IRB and PCORI within 7 calendar days of the investigator becoming aware of the event.
- Any other unanticipated problem will be reported to the IRB, the funding agency (PCORI), and the DSMC in a less urgent manner during annual continuing review and DSMC meetings.

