## **9.5 Halting Rules**

While the comparison of treatment arms is novel, the actual therapy in each treatment arms is not. All procedures are standardized, and potential adverse events are well understood. The surgery is an outpatient procedure with very low risk. Nonetheless, a continuous monitoring rule for monitoring SAE has been developed for the DSMC to ensure the SAE rate does not exceed 10%.

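### The protocol promises the DSMC a continuous SAE rule but gives no prompt DSMC route for anticipated, treatment-related SAEs

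*Protocol*

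**What the plan says.** **The rule.** Section 12.3.4 says "A continuous monitoring rule for monitoring SAE has been developed for the DSMC to ensure the SAE rate does not exceed 10" per cent. Section 9.5 (Halting Rules) repeats it: "a continuous monitoring rule for monitoring SAE has been developed for the DSMC to ensure the SAE rate does not exceed 10" per cent.

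**What counts as an SAE.** Section 9.1.3 lists two items: death, with no condition attached, and "Event requiring hospitalization (in-patient admission) related to treatment". Section 9.1 characterises the trial's events in general: "Serious Adverse Events (SAEs) are therefore those inherent to standard of care treatments". Section 2.4.1 lists readmission and, rarely, death among the known risks of surgery.

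**Who is told, and when.**
- Section 9.4.1 sends an SAE to the IRB, PCORI and the DSMC within 7 days if it "was unanticipated or unexpected, involved risk to participants or others, and was possibly related to the research procedures".
- Section 9.4.2 opens with "Anticipated AEs or unrelated SAEs will be handled in a less urgent manner", and names the DSMC among the recipients. It then provides for a summary of all adverse events, related or not, which goes to the DSMC at its yearly meetings.
- Section 9.4.3 says "Unanticipated problems that are serious adverse events will be reported to the IRB and PCORI within 7 calendar days". The DSMC is not on that list.
- Section 16.4.3 puts AEs and SAEs in the DSMC report, prepared every 6 to 12 months.
- Section 10.1 has the DSMC meet annually, or more often if it chooses.

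**The concern.** A continuous rule is useful because the count is compared with the limit as events occur. That requires the body applying the rule to learn of each countable event soon after it happens. The prompt DSMC channel is instead filtered on unexpectedness. Under 9.3.2 an event is unexpected only if its nature, severity or frequency does not fit the known risk information, so an ordinary post-surgical readmission would usually be classed as expected and kept out of that channel.

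At stake is the speed of the one numerical safety rule in the protocol. If expected surgical SAEs ran above the limit, the DSMC could first see this at its next periodic report, while patients continued to be randomised to both arms. The filter also depends on judgements of relatedness and expectedness that 9.3.1 and 9.3.2 give to the study PI, in a trial without masking (5.4.2).

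**Working it through.** The 10% is a chosen limit. The protocol gives no boundary, error rate or denominator for it, so there is no figure to reproduce. The check is a mapping of event types to DSMC routes, followed by a calculation of scale.

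**1. Routes to the DSMC by type of event**

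| Event | Section | DSMC informed |
|---|---|---|
| SAE, unexpected, with risk, possibly related | 9.4.1 | within 7 days |
| SAE handled as an unanticipated problem | 9.4.3 | not on the 7-day list |
| Unrelated SAE, e.g. an unrelated death | 9.4.2, opening | less urgently |
| Anticipated AE | 9.4.2, opening | less urgently |
| Anticipated, related SAE, e.g. readmission after surgery | not named in 9.4.1 or the opening of 9.4.2 | all-event summary, yearly (9.4.2); report every 6-12 months (16.4.3) |

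The last row is the gap: a route exists, but it is periodic. The second row is a smaller inconsistency, since an event that also meets 9.4.1 still goes to the DSMC within 7 days.

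**2. Patients randomised in one reporting interval**

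Inputs: 700 patients, about 1:1 (4.1, 12.3.3); enrollment over about 3.5 years (4.1).

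- Accrual: 700 / 3.5 = 200 per year.
- In 6 months: 200 × 6/12 = 100 patients, of whom 100 / 2 = 50 operative.
- In 12 months: 200 patients, of whom 200 / 2 = 100 operative.

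**3. SAEs arising from one interval's intake** (patients × rate)

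The protocol gives no expected SAE rate, so the rates are assumptions, set around the 10% limit.

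| Intake | at 2% | at 10% | at 20% |
|---|---|---|---|
| 6 months, all (100) | 2 | 10 | 20 |
| 6 months, operative (50) | 1 | 5 | 10 |
| 12 months, all (200) | 4 | 20 | 40 |
| 12 months, operative (100) | 2 | 10 | 20 |

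**4. How quickly a continuous rule could act (illustration only)**

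The trial's actual rule is not shown. As a stand-in, take a Pocock-type exact binomial boundary checked after every patient, with an assumed null rate of 10%, overall type I error of 0.05, and a maximum of 100, 200 or 350 patients.

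| Maximum n | Mean patients, true rate 20% | Mean patients, true rate 25% |
|---|---|---|
| 100 | 53.7 | 32.6 |
| 200 | 66.5 | 35.3 |
| 350 | 71.9 | 37.0 |

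(Runs that never cross the boundary count at the maximum n.)

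At a true rate of 20% the stand-in rule needs about 54 to 72 patients on average. That is fewer than a 12-month intake on either denominator (200 or 100), and fewer than a 6-month intake of all patients (100), though slightly more than a 6-month operative intake (50). At 25% it needs about 33 to 37, fewer than any of these. A wait for the periodic report can therefore be as long as, or longer than, the time in which a continuous rule would be expected to act.

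**The case against.** The strongest reply is that the events do reach the DSMC and that the count can be kept current. Section 9.4.2's summary covers all adverse events, and 16.4.3 places no restriction on the SAEs reported. Section 7.4.1 has subject-reported SAEs passed to the study PI and coordinator at once, and 16.1.1 has sites report every SAE to the coordinating center on awareness. The coordinating center could hold a running tally and alert the DSMC under a charter that is not shown here. The DSMC may also meet more often, and it can act on any safety concern (5.6, 10.1). Anticipated AEs in 9.4.2 could be read to include serious ones, since that section gives a death as an example of an adverse event. Finally, because 9.3.2 includes frequency, an excess of readmissions might itself be called unexpected.

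Much of this stands, and it rules out several stronger readings:
- A reader might infer that anticipated related SAEs have no route to the DSMC, or that the rule cannot be run. The periodic routes and the prompt internal capture show otherwise.
- A reader might infer that the DSMC sees these events once a year at best. Sections 16.4.3 and 10.1 allow shorter intervals.
- A reader might infer that an unrelated SAE is impossible under 9.1.3. It is not: death carries no relatedness condition, so an unrelated death is one.
- A reader might suppose that these events are nearly all that the rule counts, or convert the limit into an operative-arm rate. The protocol states neither which SAEs the rule counts nor its denominator, and gives no expected rates.
- The absence of a boundary and denominator is no fault, because the charter may hold them.

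What the reply does not remove is the last step. No section says that an anticipated related SAE is passed to the DSMC when it occurs. Reading anticipated AEs broadly puts it in the less urgent class, which confirms the point. Relying on frequency to make it unexpected requires someone to have already judged the rate excessive, which is the rule's own task.

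**Conclusion.** The point holds in this limited form: the protocol promises a continuous rule for the DSMC and states only a periodic DSMC route for anticipated, treatment-related SAEs. About 100 to 200 patients, 50 to 100 of them operative, would be randomised in one reporting interval. That figure assumes even accrual at the planned pace, equal allocation and no additional DSMC meetings. The comparison with a continuous boundary rests on an assumed rule and shows only that the delay could matter. The difference between 9.4.1 and 9.4.3 over the DSMC is a plain inconsistency with little practical effect. No excess of harm is implied; section 9.5 describes the surgery as carrying very low risk, and nothing here contradicts that.

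**What to change.** Reconcile 9.1.3, 9.4.1 to 9.4.3, 9.5, 12.3.4 and 16.4.3 as follows:

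- Forward every SAE to the DSMC on the existing 7-day clock, whatever its expectedness or relatedness.
- Record relatedness and expectedness as separate fields on each SAE report, identify the randomised arm, and word 9.1.3 to match.
- Add the DSMC to the 7-day list in 9.4.3, as in 9.4.1.
- State in 9.5 and 12.3.4 that the existing rule is applied as these reports arrive, and keep the 16.4.3 report as the periodic summary, with one interval used in 9.4.2 and 16.4.3.

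The limit, the boundary, the denominator and which SAEs enter the count remain with the DSMC and its charter.

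The cost is an amendment to the wording and a few more expedited reports. Sites already send every SAE to the coordinating center on awareness, so only the onward step to the DSMC is new.

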#### **12.3.5 Efficacy Review**

There is no planned interim analysis of study efficacy outcomes, as all interventions are standard of care.

### **12.4 Model Assessment and Sensitivity Analyses**

**Treatment of Crossovers and Missing Data:** Although we expect that a significant but manageable number (8% in our observation study) of patients receiving PT only (non-operative treatment) will request surgery (operative treatment), our analytical strategies presented below will also account for the potential of high crossover rates. We order our analyses as follows: First, our primary model will be a strict intent-to-treat analysis, wherein patients who choose to crossover to surgical treatment will have post-surgical outcomes attributed to the treatment arm as randomized. Second, we will treat crossovers as dropouts at the time of crossover and treat the resulting data as missing to be evaluated according to Rubin's classification of missing data and their appropriate analyses. Our sample size estimates illustrate that these analyses have good power, even in the presence of significantly high rates of missing/crossover data, and we believe they will provide the best estimates of treatment and covariate effects. Third, we will assign a treatment effect of zero to each crossover patient. This approach assigns an appropriate penalty to the non-

surgical treatment for having failed that patient. This approach will produce appropriately conservative statistical tests and preserve study power.

**Assessing Model Fit:** The assessment of model fit is indispensable for model development and implementation. Non-linear predictor rescaling, in the form of restricted cubic splines, will be evaluated and models compared using Akaike criteria. Multivariate association and missing data patterns will be evaluated using trellis graphics and clustering algorithms. Such summary analyses may inform sensitivity analyses with respect to modeling assumptions, rescaling of predictors (e.g., restricted cubic splines), and co-linearity. We will repeat these analyses for the secondary outcome (ASES-SF). Along with standard goodness-of-fit and residual analysis, we will perform model validation and calibration using bootstrap methods as discussed in Harrell.

**Sensitivity Analyses:** We will not rely only on Gaussian parametric modeling, as our primary mixed effects model will be cross-checked using a proportional odds regression comparing treatment effects after adjusting for baseline SPADI, study site, age, tear size, fatty infiltration, and their interactions. We will conduct full information analysis and no levels will be combined. Thus for k unique SPADI change scores, there will be k-1 levels. In addition to the primary contrast of operative versus non-operative treatment and the primary covariates, *a priori* selected independent variables include those noted in Section D.6. In model development, descriptive statistics and graphical displays of outcomes and predictor variables will be examined. Under this category we also note our plans the sequential modeling under MCAR, MAR, and MNAR missing data analyses described below. We will also perform a sensitivity analysis of the time from baseline to a 10 point (MCID) change in SPADI using Cox regression, and the binary outcome of achieving a 10-point change in SPADI, and 30% and 50% improvement in outcome scores (success) versus failure using logistic regression. We will repeat sensitivity analyses for secondary outcomes.

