### 2.2 Rationale

Our interest is in treatment for chronic degenerative rotator cuff tears. Therefore, patients  $\geq 50$  years of age will be eligible. Acute traumatic tears will be excluded because they are treated surgically as per expert opinion. Since rotator cuff specific literature on what constitutes trauma is unavailable, we draw from the osteoporosis literature and use the criteria proposed by Mackey et al. Patients reporting severe trauma will be excluded whereas those with low velocity trauma will still be included since the low velocity trauma likely exacerbated a pre-existing rotator cuff tear. Both partial-thickness and full-thickness tears will be included since the dilemma of operative versus non-operative treatment applies to both settings. Patients with Grade IV fatty infiltration will not be included since these patients may not be candidates for surgery in clinical practice. Patients with isolated subscapularis tears will also be excluded since these tears are usually traumatic and treated surgically. Detailed inclusion and exclusion criteria are presented in Sections 5.1 & 5.2.

Both operative and non-operative treatments are standards of usual care. Operative treatment will include arthroscopic rotator cuff surgery. The standards of care/protocol for operative treatment are included in Supplemental Materials. As in usual clinical practice, patients will have post-operative physical therapy after surgery. The post-operative physical therapy lasts for approximately 4 months. A standardized post-operative physical therapy regimen for this trial is included in Supplemental Materials.

Patients randomized to non-operative treatment will only receive physical therapy. This usually lasts for approximately 3 months. A standardized non-operative physical therapy regimen for this trial is included in Supplemental Materials.

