## **4 STUDY DESIGN**

### **4.1 Primary Study**

This is an unblinded, multi-center, pragmatic randomized controlled clinical trial of operative versus non-operative treatments for atraumatic rotator cuff tears. A sample size of 700 patients will be enrolled with approximately equal numbers of patients randomized to operative treatment (surgery + post-op physical therapy) and non-operative treatment (physical therapy only without surgery). Both treatments are current standards of care. The duration of enrollment is expected to last approximately 3.5 years. For the main study and analysis, a 12-month follow-up is needed, with the duration of the primary study lasting for approximately 5 years.

Upon enrollment at baseline, patients will fill out study questionnaires, undergo a brief physical examination, and, if applicable, have a research MRI. Follow-up for the primary study will be performed via questionnaires at 3, 6, and 12 months.

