#### **5.4.2 Masking Procedures**

Intervention arms will not be masked, as this is a non-blinded study.

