### **6.3.1 Surgery**

Study surgeons at each recruiting site will administer the surgical rotator cuff repair/debridement for those subjects in the operative arm of the study recruited from their site. Surgery should be scheduled to occur within 8 weeks after randomization to the operative treatment arm. If surgery occurs later than 8 weeks after randomization, it will be considered a protocol deviation.

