## **7.4 Follow-Up**

### **7.4.1 Follow-Up Questionnaires ( $\pm$ 4-6 weeks from follow-up time point)**

Subjects enrolled in the study and randomized to treatment will be sent follow-up questionnaires at the following intervals:

- 3 months after randomization
- 6 months after randomization
- 12 months after randomization
- Annually thereafter for years 2-10 (for the sub-study)

Questionnaires can be completed on paper or electronically (via tablet or computer), per the subject's preference.

The target window for completion of follow-up questionnaires is -4 weeks/+6 weeks from the ideal follow-up time point, based on date of randomization. For example, if a subject was randomized to treatment on June 1st, the ideal date for completion of his/her 3-month follow up questionnaire would be Sept 1st (+3 months); the lower window would be August 1st (ideal date minus 1 month) and the upper window would be Oct 14th (ideal date + 6 weeks). Questionnaires will be sent out no earlier than the lower window date.

A concerted, systematic effort will be made to obtain completed questionnaires by the target upper window date (including up to 3 contacts by research staff and a PI call, if needed). However, it will not be considered a protocol deviation if a patient questionnaire is completed after the upper window date. It will only be considered a protocol deviation if a patient questionnaire is not completed at all for a given time point. The date a questionnaire was completed in relation to the ideal date for a given time point will be taken into account during data analysis.

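### Cox regression for time to a 10-point SPADI change is fitted to an outcome seen only at three questionnaires, and it measures speed of first response rather than checking the 12-month endpoint

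*Protocol*

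**What the plan says.** Section 12.4 of the Protocol lists, under sensitivity analyses, a "sensitivity analysis of the time from baseline to a 10 point (MCID) change in SPADI using Cox regression". The same sentence adds logistic regression for achieving a 10-point change and for 30% and 50% improvement, without naming a time point. The section does not say whether *change* means a fall in SPADI, and it repeats the sensitivity analyses for secondary outcomes.

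On when SPADI is seen, section 4.1 states: "Follow-up for the primary study will be performed via questionnaires at 3, 6, and 12 months". Section 7.4.1 adds: "The target window for completion of follow-up questionnaires is -4 weeks/+6 weeks from the ideal follow-up time point, based on date of randomization". Later forms are kept, since "it will not be considered a protocol deviation if a patient questionnaire is completed after the upper window date". The completion date relative to the ideal date "will be taken into account during data analysis", but the method is not given.

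On the arms, section 5.4.2 notes that "this is a non-blinded study". Section 6.3.1 says: "Surgery should be scheduled to occur within 8 weeks after randomization to the operative treatment arm". Section 2.2 adds: "The post-operative physical therapy lasts for approximately 4 months".

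**The concern.** The moment at which a patient first improves by 10 points is never observed. It is known only to lie between two questionnaires that are three or six months apart. A continuous-time Cox model needs an exact time, and the only dated quantity available is when the form was completed. The ordering of events within a visit would then be the order in which forms came back.

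A second issue is separate. Time to first 10-point change counts the first crossing and ignores everything afterwards. The primary endpoint is the 12-month change. With surgery at the 8-week limit, the 3-month form arrives about 5 weeks after the operation (13 − 8), and about 4 months of rehabilitation covers the 3-month form even if surgery is immediate. The arms may therefore differ in early recovery independently of the 12-month result.

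At stake is how the analysis would be read. A hazard ratio near 1 or reversed, beside a clear 12-month benefit, would look like a failed robustness check. A significant one beside a null primary result would look like support.

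**Working it through.** **Inputs from the Protocol.** 350 per arm and two-sided 0.05 (12.3.3); event threshold and effect size 10 points (12.3.2); SDs 21.55 (n=45) and 19.14 (n=27) (12.3.1); visits at 3, 6 and 12 months, taken as weeks 13, 26 and 52; window −4 to +6 weeks (7.4.1).

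**Reproducing the plan's own figure.** Pooled SD = √[(44×21.55² + 26×19.14²)/70] = √427.98 = 20.69. For a difference of 10 and 90% power, the normal formula gives n = 2(1.96+1.282)²×427.98/100 ≈ 90 per group; the noncentral t gives power 0.900 at 91. The stated 91 per group reproduces. The Protocol gives no figure for the Cox analysis.

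**What the window does to ranking.** The three windows span weeks 9–19, 22–32 and 48–58. They do not overlap, so on-time forms keep the visit order. Within a window of up to 10 weeks, event order is decided by return date alone.

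**Simulation assumptions not in the Protocol.** SPADI changes at the three visits are trivariate normal with SD 20.7 and correlation 0.6 (range 0.4–0.8); 10% are missing at each visit; non-operative mean changes are −15/−20/−25. The event is the first observed change of −10 or lower. Cox uses Efron ties, with 400–1000 trials per case.

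**(a) Identical SPADI courses, equal return timing.** Cox on return dates rejects in 4–5% of trials.

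**(b) Identical SPADI courses, operative forms later by a fixed lag.**

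| Lag | Returns over −4 to +6 weeks | Returns over 0 to 6 weeks |
|---|---|---|
| 0.5 week | 10% (HR 0.94) | 21% (HR 0.91) |
| 1 week | 26% (HR 0.89) | 56% (HR 0.84) |
| 2 weeks | 71% (HR 0.82) | 96% (HR 0.74) |

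The full-window figures rest on 500 trials; simulation error at 26% is √(0.26×0.74/500) ≈ 2 points.

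**(c) Equal 12-month means, slower early operative recovery, no lag.** With the operative arm 5 or 10 points behind at 3 months only, Cox rejects against it in 27% (HR 0.89) or 74% (HR 0.81; 60–81% over correlations 0.8–0.4). Nominal visit times give 24% and 71%, so return dates are not the cause.

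**(d) Operative arm truly 10 points better at 12 months, no lag.** The 12-month t-test rejects in 100%.

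| Operative means at 3/6/12 months | Cox, return dates | Cox, nominal times | Discrete-time, one treatment term |
|---|---|---|---|
| −15/−20/−35 | 10% (HR 1.06) | 16% (HR 1.09) | 19% (HR 1.09) |
| −10/−20/−35 | 9% (HR 0.95) | 5% (HR 0.98) | 7% (HR 0.98) |
| −5/−20/−35 | 44% (HR 0.86, wrong direction) | 23% (HR 0.90) | 30% (HR 0.89) |

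About 88% of patients have an event in these cases, so the final visit can add little.

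**12-month responder comparison in (d).** The expected proportions are Φ(15/20.7) = 0.77 and Φ(25/20.7) = 0.89. With 315 observed per arm (350×0.9), the simulated proportions 0.765 and 0.886 give SE = √[(0.765×0.235 + 0.886×0.114)/315] = 0.030 and z = 0.121/0.030 ≈ 4.1. Power is about 98%, matching the simulated 98%.

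**Discrete-time model under (a) or (b).** It rejects in 6.8% of 500 trials (simulation error about 1 point) whatever the lag, because return dates do not enter.

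**The case against.** The Protocol never says that return dates are the event times. Event time, ties and censoring are details that a statistical analysis plan may settle, and with nominal visit times and Efron ties the false-positive rate is 3–3.5%. That stands. What the Protocol itself fixes is a continuous-time model for data from three visits, and 7.4.1 commits to using completion dates.

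A reader might infer that visit-based observation or a wide window alone creates false effects. It does not: equal timing gives 4–5%. The lag is essential, and no section reports or predicts one. The coordinating center runs follow-up centrally, on one schedule dated from randomization, with the same reminders for both arms. An unblinded trial with different treatment timetables makes a lag possible, not established.

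A reader might also infer that a visit-based model would recover a missed 12-month effect. It would not: case (d) shows 7% and 19% when the operative arm is at most 5 points behind at 3 months, and the wrong direction when it is 10 points behind. Speed of response is a legitimate but different question, and slower early recovery would be a real treatment difference, not an artefact. The early means are assumptions, because 12.3.1 gives 12-month values only.

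Finally, 12.4 already plans a logistic responder analysis and names proportional odds regression as the cross-check of the primary model. That limits the harm, although the logistic analysis has no stated time point.

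**Conclusion.** The point holds as a minor one with two separate parts.

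First, the event time is interval-censored and Cox regression does not suit it. If completion dates are used and the arms differ in return timing, false positives rise to about 10%, 26% and 71% for lags of 0.5, 1 and 2 weeks over the full window. Both conditions are assumptions.

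Second, time to first 10-point change is not a check on the 12-month endpoint. With a true 10-point benefit at 12 months, the Cox hazard ratio ran from 1.06 down to 0.86 depending on the assumed 3-month means. This comes mainly from the endpoint: return dates change the size (44% against 23% in the last row of (d)) but not the pattern.

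The percentages move with the assumed means, correlation and delays. The documents do not support any inference that the primary mixed-model result or the sample size of 700 is at risk.

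**What to change.** In 12.4:

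- Replace the Cox model with a discrete-time model (complementary log-log link) or an interval-censored model, with visit as a factor, a treatment-by-visit term and baseline SPADI as covariate.
- State that *change* means a fall in SPADI of at least 10 points.
- Label the result as speed of first response, not as a check on the 12-month endpoint.
- Set the planned logistic analysis of a 10-point improvement at 12 months as the responder cross-check, and report the proportions by arm at 3 and 6 months as well.

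The treatment-by-visit term shows where the arms diverge. Its 12-month coefficient still concerns only patients who have not yet responded, so it does not replace the responder comparison.

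The cost is a few sentences and a different regression command on data already being collected. There will be no single hazard ratio, and the visit-indexed version does not use exact completion dates, which 7.4.1 says will be considered. An interval-censored model can keep them as interval limits.
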